#### Usability

Usability of the TeACH System and its control arm are assessed post interaction (ie, immediately after receiving the allocated feedback and resources) and 1 week after the interaction through the After Scenario Questionnaire, a 3-item measure of usability [57].

### Data Analyses

#### Overview

Descriptive analyses will be conducted to characterize the sample, primary outcomes, and usability ratings of the TeACH System. To assess changes in the engagement outcomes over time and account for missing data, linear or generalized linear mixed effects regression models will examine differences in responses to the baseline, postinteraction, and maintenance questionnaires. Demographic variables and existing DMH use, as well as their interactions with time, will be examined as covariates to assess differential engagement outcomes based on these variables.

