### Procedures

#### Study Design

The study design is a pilot feasibility randomized controlled trial. The participant focus is teen patients in PPCs with anxiety. While universal anxiety screening is recommended [19], pediatric anxiety has a long-standing history of being underrecognized and often untreated [47-49]. Participants first answer initial screening eligibility questions (ie, age, clinic location, and ability to complete and read surveys in English), followed by completing a digital assent. While a waiver of guardian consent was obtained from the institutional review board, participants are able to “opt in” to have a guardian provide consent in English or Spanish, should they elect to do so. Following assent and optional guardian permission, participants complete a brief demographic survey, indicate their preference for future contact (ie, text message or email), and complete a brief assessment of the primary outcomes (Measures section). All participants then complete the Kiddie-Computerized Adaptive Tests (K-CAT) Anxiety Module [50] to ensure eligibility (ie, a score >29 and indicating mild or greater anxiety symptoms). Participants who do not meet these criteria are excluded and offered access to a publicly available, digital evidence-based workbook for teens [43,44]. Participants who do meet the criteria for mild or greater symptoms of anxiety are randomized into either the control arm (digital evidence-based workbook [43,44]) or the Intervention Arm (TeACH System Feedback and Resources). Randomization is automated through the Research Electronic Data Capture (REDCap, Vanderbilt University) platform, and study staff members are blind to allocation. Following a review of these resources, all participants are invited to complete an immediate follow-up survey. One week following this interaction, participants are invited to complete the same follow-up survey. Figures 1 and 2 display the study design flow.

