#### Inclusion and Exclusion Criteria

For study inclusion, participants must be (1) receiving care at the specified clinics at UIC or RUSH; (2) between 13 and 17 years of age; and (3) able to speak and read in English. These inclusion criteria are determined by teen self-report (ie, answering 3 screening questions based on these criteria). Following assent and completion of a demographics and engagement survey (Measures section), final inclusion criteria are assessed based on responses to the K-CAT Anxiety Module. Namely, to be randomized, participants must also meet criteria for mild or greater symptoms of anxiety (ie, K-CAT Anxiety Module score >29) [50]. There are no assessments for comorbidities, nor any exclusion criteria beyond not meeting the inclusion criteria noted above.

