#### Sample Size and Power

Power and sample size computations were based on previously published work [58,59]. Conservative estimates of sample sizes were estimated (ie, anticipating a 15% attrition rate on the follow-up survey), which indicated that 300 patients were deemed appropriate to examine the initial TeACH System use (ie, K-CAT Anxiety module, feedback, and resources) after being invited during their PPC appointment. With an expected 15% attrition rate for the follow-up questionnaire 1 week later, we would be adequately powered for within-subjects (pre vs post using the main effect of time) and between groups comparisons (TeACH System vs Control condition using treatment by time interaction). For within-subjects comparison, our proposed sample size is overpowered such that we should exceed 90% power to detect differences generally considered to be moderate in size (*d*=0.5) with a sample size exceeding approximately 70 participants. To detect within-subjects differences from baseline to endpoint equivalent to *d*=0.34 for the engagement outcomes, we would require a sample size of approximately 136 for 95% power. As such, our proposed sample is more than adequate for the planned within-subjects comparisons. For between-group comparisons with the anticipated 15% attrition rate, we should have 95% power to detect differences generally considered moderate in size (*d*=0.5) with 240 participants. With our proposed sample size of 300 participants, we will have 80% power to detect smaller differences equivalent to *d*=0.34.

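### The baseline K-CAT Anxiety score, held for every randomized teen before allocation, is not among the named model covariates; prespecifying it with its time interaction is a low-cost, conditional improvement

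*Protocol article*

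**What the plan says.** The Overview under Data Analyses states the model: "linear or generalized linear mixed effects regression models will examine differences in responses to the baseline, postinteraction, and maintenance questionnaires". The mixed model is also meant to deal with missing data. The covariates follow: "Demographic variables and existing DMH use, as well as their interactions with time, will be examined as covariates", with the aim "to assess differential engagement outcomes based on these variables". The K-CAT score is not mentioned there.

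The score is nevertheless available. In Study Design, before randomization: "All participants then complete the Kiddie-Computerized Adaptive Tests (K-CAT) Anxiety Module". Under Inclusion and Exclusion Criteria, "final inclusion criteria are assessed based on responses to the K-CAT Anxiety Module", and to be randomized "participants must also meet criteria for mild or greater symptoms of anxiety (ie, K-CAT Anxiety Module score >29". The same section says that comorbidities are not assessed. The Measures section adds only demographics, the four primary-outcome items and usability.

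Sample Size and Power identifies the between-group test: "TeACH System vs Control condition using treatment by time interaction".

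**The concern.** The population is defined by anxiety severity, and all four primary outcomes concern what a teen understands or does about anxiety. Severity is therefore a natural candidate for predicting how answers change and who returns the 1-week survey. The plan examines demographics and earlier use of digital tools, each with a time interaction, but not the one severity score that is complete by design.

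Two things could be at stake:

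- **Precision.** If severity predicts change, leaving it out leaves explainable variance in the treatment-by-time contrast.
- **Missing data.** A likelihood-based mixed model handles loss under missing at random, given what is in the model. If severity drives both loss and change beyond what the earlier answers carry, a model without it can be biased.

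Both depend on associations that the article does not report.

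**Working it through.** The article gives no figure for covariate adjustment and no correlation of K-CAT with outcome or loss, so there is no plan figure to reproduce. Every association below is an assumption.

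**1. Which form of adjustment can matter.** Write teen *i*'s answer at time *t* as a mean for arm and time, plus b·K (constant over time), plus g(t)·K (zero at baseline), plus error, where K is the K-CAT score. The between-group contrast compares changes from baseline. In a change score b·K cancels and only g(t)·K remains. A main effect estimates b; K-CAT-by-time estimates g(t). Baseline answers are already in the model as the first wave.

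**2. Size if severity predicts change.** If r is the correlation of K-CAT with change, the standard error is multiplied by √(1 − r²):

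| assumed r | ratio | reduction |
|---|---|---|
| 0.1 | 0.995 | 0.5% |
| 0.2 | 0.980 | 2.0% |
| 0.3 | 0.954 | 4.6% |
| 0.4 | 0.917 | 8.3% |
| 0.5 | 0.866 | 13.4% |

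Randomized teens all score above 29. That narrows the K-CAT range and tends to push r towards the top rows.

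**3. Check in a three-wave model.** Simulation with 300 teens, unstructured covariance, no true treatment effect and 200 replicates per cell. With 15% random loss at week 1, the mean model standard error of the week-1 treatment-by-time contrast was:

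| K-CAT effect, constant / on change (SD) | no K-CAT | main effect | plus K-CAT-by-time |
|---|---|---|---|
| 0.3 / 0 | 0.1144 | 0.1145 | 0.1144 |
| 0.5 / 0 | 0.1047 | 0.1039 | 0.1046 |
| 0.3 / 0.2 | 0.1122 | 0.1125 | 0.1094 |
| 0 / 0.3 | 0.1228 | 0.1233 | 0.1176 |

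The main effect does essentially nothing. The interaction helps only in the last two rows:

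- 1 − 0.1094/0.1122 = 2.5%
- 1 − 0.1176/0.1228 = 4.2%

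**4. Missing data.** Same model, but week-1 loss depends on K-CAT. The log-odds of loss are −1 at average severity, that is 1/(1 + e) = 27% loss. They rise by 1 per unit of K-CAT in one arm and fall by 1 in the other. Mean estimate (truth 0; simulation error about 0.13/√200 = 0.009):

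| constant / on change (SD) | no K-CAT | main effect | plus K-CAT-by-time |
|---|---|---|---|
| 0.3 / 0 | −0.027 | 0.007 | 0.004 |
| 0.5 / 0 | −0.039 | 0.007 | −0.003 |
| 0.3 / 0.2 | −0.103 | −0.030 | 0.000 |
| 0 / 0.3 | −0.099 | −0.062 | −0.021 |

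For scale, a bias of 0.10 SD is 0.10/0.34 = 29% of the smaller effect, d=0.34, named in Sample Size and Power. The scenario is deliberately unfavourable: loss exceeds the planned 15% and runs in opposite directions by arm.

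**5. Price of the interaction when it is not needed.** In the first two rows of step 4, the model standard error rose from 0.1200 to 0.1232 (2.7%) and from 0.1088 to 0.1124 (3.3%). With random loss there was no visible price (0.1144 in both).

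**The case against.** The strongest reply is that no error has been shown. The Overview is a short passage in a condensed article, and the full adjustment set may stand in an analysis plan that is not shown. The sentence on covariates is about differential engagement; it is not presented as a precision-adjustment set and does not claim to be exhaustive. The randomized comparison is valid without K-CAT. All of this stands, and it limits the point to an improvement. What remains is that the article does name a set, gives it time interactions, and leaves severity out, although severity serves the stated aim at least as well as demographics do.

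A second reply also stands: the benefit is conditional. Nothing in the article links K-CAT to change or to loss, the eligibility cut restricts its range, and a main effect alone would achieve almost nothing for precision.

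Third, digital-tool use is answered yes, no or unsure, which points to a generalized linear model. With a logit link, for example, adding a predictive covariate changes the effect being estimated to a conditional one and need not shrink its standard error. The precision argument therefore applies to the three Likert items analysed with a linear model.

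A reader might go further and infer that the planned estimates do lose precision, and by a known amount of power. The documents do not support this: no correlation is given, and a two-group calculation with a shrunken variance does not describe the planned three-wave model.

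**Conclusion.** The point holds as a modest, conditional improvement to a stated choice. It does not correct an error. The K-CAT score is measured before allocation, held for every randomized teen, and not named among the covariates.

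If severity shifts change by 0.2 to 0.3 SD, K-CAT with K-CAT-by-time trims the standard error of the treatment-by-time contrast by about 2.5% to 4%. If severity also drives loss differently by arm, a bias near 0.10 SD falls to between 0.00 and 0.02 SD. If severity predicts neither change nor loss, there is nothing to gain. These figures rest on assumed associations in a linear model for continuous outcomes.

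A reader might take the 42 one-week completions among 80 randomized teens, reported in Results, as an attrition rate that makes the missing-data argument urgent. The article does not support that. It is a snapshot during recruitment, and some teens may not yet have been due for the survey.

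**What to change.** Extend the covariate sentence in the Data Analyses Overview along these lines: the continuous baseline K-CAT Anxiety score and its interaction with time will be included in every primary-outcome model, fixed in advance and not selected on statistical significance. For the yes/no/unsure item on digital-tool use, add that the adjusted treatment effect is conditional on the covariates.

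The interaction is the part that matters. The main effect alone should not be offered as a gain in precision. The form matches what the Overview already plans for its other covariates.

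The cost is one sentence and a few degrees of freedom per model, with no new data collection. If severity governs loss but not change, the standard error may rise slightly (about 3% in the simulation above).

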#### Sample Size and Power

Power and sample size computations were based on previously published work [58,59]. Conservative estimates of sample sizes were estimated (ie, anticipating a 15% attrition rate on the follow-up survey), which indicated that 300 patients were deemed appropriate to examine the initial TeACH System use (ie, K-CAT Anxiety module, feedback, and resources) after being invited during their PPC appointment. With an expected 15% attrition rate for the follow-up questionnaire 1 week later, we would be adequately powered for within-subjects (pre vs post using the main effect of time) and between groups comparisons (TeACH System vs Control condition using treatment by time interaction). For within-subjects comparison, our proposed sample size is overpowered such that we should exceed 90% power to detect differences generally considered to be moderate in size (*d*=0.5) with a sample size exceeding approximately 70 participants. To detect within-subjects differences from baseline to endpoint equivalent to *d*=0.34 for the engagement outcomes, we would require a sample size of approximately 136 for 95% power. As such, our proposed sample is more than adequate for the planned within-subjects comparisons. For between-group comparisons with the anticipated 15% attrition rate, we should have 95% power to detect differences generally considered moderate in size (*d*=0.5) with 240 participants. With our proposed sample size of 300 participants, we will have 80% power to detect smaller differences equivalent to *d*=0.34.

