## Results

This study received funding from the National Institute of Mental Health on September 13, 2021 (K08 MH125069), and began recruiting at UIC in July 2024 and at Rush in August 2024. Earlier funded activities informed the design and implementation planning for the current trial [23,32,42,54]. To date, 122 teens have assented to complete study activities, 80 have been randomized (an additional 24 teens have had subthreshold anxiety symptoms and were therefore not randomized), and 42 teens have completed the one-week follow-up assessment. We expect data collection to be completed by August 2025.

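### The between-group power uses 300 without saying whether that counts teens screened with the K-CAT or teens randomized, and allows nothing for the K-CAT exclusion that comes first

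*Protocol article*

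**What the plan says.** Sample Size and Power introduces the target thus: "300 patients were deemed appropriate to examine the initial TeACH System use (ie, K-CAT Anxiety module, feedback, and resources) after being invited". The only loss it names is at the 1-week survey: "anticipating a 15% attrition rate on the follow-up survey". The between-group test is described as "TeACH System vs Control condition using treatment by time interaction". For that test the section claims 95% power at d=0.5 with 240 participants, and then: "With our proposed sample size of 300 participants, we will have 80% power to detect smaller differences", the effect being d=0.34.

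Study Design has every assented teen take the K-CAT Anxiety Module before randomization and excludes those who do not score above 29. Inclusion and Exclusion Criteria says the same: "to be randomized, participants must also meet criteria for mild or greater symptoms of anxiety".

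Results gives the flow so far. There were 122 assents, of whom "80 have been randomized (an additional 24 teens have had subthreshold anxiety symptoms and were therefore not randomized".

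Nowhere does the article attach the word randomized to the 300, and it mentions no inflation for teens screened out.

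**The concern.** The use of the system that the 300 are meant to inform begins with the K-CAT, and the K-CAT is the gate in front of randomization. The between-group comparison includes only teens who pass that gate. A number counted at the K-CAT must therefore be reduced for screen failures before it can serve as the sample for comparing arms, and the paragraph makes no such reduction.

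At stake is the claim of 80% power at d=0.34, and possibly the point at which enrolment ends. Recruitment was already under way when the article was written. If the 300 were counted at the K-CAT, the randomized comparison would be roughly a quarter smaller than the power statement assumes.

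**Working it through.** **Inputs from the article.** N = 300; attrition 15%; d = 0.34 and 0.5 (Sample Size and Power). 122 assented, 80 randomized, 24 subthreshold (Results).

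**Assumptions, not stated in the article.** Two-sided alpha 0.05; 1:1 allocation; a two-sample comparison of completers with SD 1. The 104 teens with a known K-CAT result are inferred as 80 + 24.

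**Formula.** With n analysed in total, power = Φ(d × √(n/4) − 1.96). The d detectable with 80% power = 2 × (1.96 + 0.8416)/√n. A noncentral t check changes power by less than half a percentage point at n = 255, 204 and 196, and by about half a point at n = 167.

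**1. The plan's own figures.**
- 240 at d=0.5: 240 × 0.85 = 204; 0.5 × √51 − 1.96 = 1.61; power 94.6%. This agrees with the stated 95%.
- Within-subjects at d=0.34 and 95% power: 115 pairs by the paired t; 115/0.85 = 135.3, so 136. This agrees with the stated figure of about 136.
- 300 at d=0.34: 300 × 0.85 = 255; 0.34 × √63.75 − 1.96 = 0.755; power 77.5%. The stated 80% is not quite reached. It would need 272 completers, which is 320 randomized at 15% attrition.

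The two figures that reproduce do so with attrition as the only loss. Adding the K-CAT loss to the 240 gives 240 × 80/104 × 0.85 = 157 and power of about 88%, which does not match 95%. So the power figures were evidently computed for randomized teens.

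**2. Size of the gate.** 24/104 = 23.1% fail (95% Wilson interval 16% to 32%); 80/104 = 76.9% pass.

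**3. Between-group power by what the 300 counts.**

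| 300 counts | Randomized | Analysed at 15% loss | Power, d=0.34 | Power, d=0.5 | Detectable d, 80% power |
|---|---|---|---|---|---|
| Randomized teens | 300 | 255 | 77% | 98% | 0.35 |
| K-CAT takers | 300 × 80/104 = 231 | 196 | 66% | 94% | 0.40 |

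For the second row: 0.34 × √(196.2/4) − 1.96 = 0.42, giving 66%; 5.603/√196.2 = 0.40.

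Using the ends of the interval for the failure rate: 300 × 0.84 × 0.85 = 214 analysed gives 70%, and 300 × 0.68 × 0.85 = 173 gives 61%.

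**4. Screening needed to randomize 300.** 300/(80/104) = 390 K-CAT completers.

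**5. Lower bound.** If the 300 were assents and every assented teen not yet randomized were lost, 300 × 80/122 = 197 would be randomized and 167 analysed, with 59% power at d=0.34 and 90% at d=0.5. Randomizing 300 would then take about 458 assents. This counts as lost the 122 − 80 − 24 = 18 teens whose status is not given.

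**6. Within-subjects.** Power at d=0.34 is above 99% with either 196 or 167 completers.

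**The case against.** The strongest reply is that the 300 are simply the randomized teens. The sentence lists three components (K-CAT, feedback and resources), and teens below the cut-off are offered only the public workbook. Only randomized teens reach the feedback and resources allocated to an arm. The rest of the paragraph treats 300 as a trial sample with follow-up loss only, and its companion figures reproduce on that basis.

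This stands as a possible reading. A reader might infer that the article defines the 300 as teens invited to take the K-CAT, so that the number cannot also be the randomized sample. The wording does not go that far. Nor does it settle the matter the other way. Under Study Design and Control Condition, the TeACH feedback and resources belong to the intervention arm, so a strict reading of all three components would make the 300 a single arm. The counting stage is left open.

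Three further points have force.
- The drop should be measured from 77.5% by the same method, not from the stated 80%. The gate accounts for 77.5 − 66.3 = 11.2 percentage points.
- The planned mixed models use all three time points, and the 15% loss applies only to the last. Actual power could exceed the completers-only figures, so the gap between 77% and 80% is not proof of a calculation error. Losing 23% of the sample would still lower power under such a model.
- This is a pilot feasibility trial, and power at d=0.5 hardly changes.

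It can also be said that a condensed article leaves the recruitment stop to the full protocol, and that the flow diagrams are not shown. That is fair for operational detail. But the article itself states the 300, the attrition and the power, and these cannot be read together without knowing what the 300 counts.

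**Conclusion.** The point holds as an undefined denominator with a material effect on one stated figure. The between-group power uses 300 with no allowance for the K-CAT exclusion, while the sentence introducing the 300 describes use of the system from the K-CAT onward. If the 300 are randomized teens, power at d=0.34 is about 77%. If they are K-CAT takers, it is about 66% (61% to 70% over the interval for the failure rate), with 80% power only at d of about 0.40. The effect is confined to the smaller between-group difference: power at d=0.5 is still about 94% and within-subjects power is above 99%.

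These figures rest on two-sided alpha 0.05, 1:1 allocation, a simple two-group comparison of completers, and the interim pass rate continuing.

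Two stronger conclusions are not supported. The article does not say that recruitment will stop at 300 screened teens. The 59% and 458 assents are a lower bound only, because some of the 18 unexplained teens may still be in process: recruitment was continuing, and Study Design allows optional guardian permission before the K-CAT.

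**What to change.** Revise the Sample Size and Power paragraph in one of two ways.

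- If 300 is the number to be randomized, say so, and say that the recruitment stop is counted at randomization. Add the screening this implies: about 390 K-CAT completers at the interim pass rate.
- If 300 is the number entering the K-CAT, restate the between-group power for about 231 randomized and 196 analysed: about 66% at d=0.34, or 80% at d of about 0.40.

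In either case give the alpha, the allocation ratio and the model behind the power figure, so that the 80% can be checked. If an assent-based figure is quoted, label it a lower bound.

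The cost is one corrected paragraph. The first option may also mean more screening than a count of 300 at the K-CAT would have needed. The second means accepting a less favourable power statement.

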#### Primary Outcomes

The primary outcomes are administered within REDCap and are assessed at 3 time points for all participants: (1) baseline: following assent and before administration of the K-CAT; (2) post interaction: immediately after receiving the allocated feedback and resources; and (3) maintenance: 1 week following the interaction. The primary outcomes are discrete variables focusing on individual-level barriers to mental health care (ie, symptom understanding, confidence to act [24-26]) and engagement with DMH (ie, likelihood to use DMH for anxiety, actual DMH use). Namely, through a questionnaire created for this study, participants rate on a Likert scale (1=not at all to 5=completely): (1) anxiety *understanding* (ie, “I understand what anxiety is.”); (2) *confidence to act* (ie, “I feel confident I can do something if I feel anxiety.”); and (3) *likelihood* to use digital tools for anxiety (ie, “If I feel anxiety, I would use a digital tool to help (app, website, and reel or video).”). Following this, participants indicate whether they have used a digital tool for their anxiety before (ie, yes, no, and unsure).

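### The arm comparison is an interaction with baseline among the responses and no stated baseline adjustment: valid, but less precise than a baseline-adjusted contrast

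*Protocol article*

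**What the plan says.** The section Sample Size and Power names the arm test: "between groups comparisons (TeACH System vs Control condition using treatment by time interaction". The Data Analyses overview says that "linear or generalized linear mixed effects regression models will examine differences in responses to the baseline, postinteraction, and maintenance questionnaires", so baseline is one of three modelled responses. On covariates it says "Demographic variables and existing DMH use, as well as their interactions with time, will be examined as covariates". The baseline scores of the Likert outcomes are not listed there, and no equal-baseline constraint is mentioned.

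The Primary Outcomes section times the first assessment as "baseline: following assent and before administration of the K-CAT". The Study Design section places randomization after the K-CAT, so every baseline score precedes allocation. The Likert outcomes are three single items scored 1 to 5 (understanding, confidence to act, likelihood of using a digital tool).

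For between-group power the article states that "we should have 95% power to detect differences generally considered moderate in size" (d=0.5, 240 participants) and that, with 300, "we will have 80% power to detect smaller differences equivalent to *d*=0.34". Both figures are set against 15% attrition at the 1-week questionnaire.

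**The concern.** Because baseline is measured before randomization, the two arms have the same expected baseline mean. A model that still estimates a baseline arm difference, and then tests the interaction, subtracts a noisy estimate of a quantity known to be zero in expectation. The result is unbiased but carries avoidable variance, most of all when baseline predicts follow-up weakly. Below r=0.5 a difference in changes is less precise than comparing follow-up scores and ignoring baseline altogether.

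The power statement is also not tied to this contrast. The power of a difference in changes depends on r unless d is scaled by the SD of change, and the article gives neither r nor the scale of d.

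At stake is precision in a trial with little slack at d=0.34. The validity of the comparison is not in question.

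**Working it through.** **Inputs.** From Sample Size and Power: 300 randomized, 15% missing at 1 week (300 × 0.85 = 255 completers), d=0.34 with 80% power; 240 participants (240 × 0.85 = 204 completers), d=0.5 with 95% power. Assumed because not stated: 1:1 allocation, two-sided 5% test, r over a range, and d in raw-score SD units, with change-SD units as the alternative.

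**Step 1: the article's figures.** A plain two-sample comparison has SE = 2/√N in SD units and power = Φ(d/SE − 1.96).
- d=0.5, 204 completers: 94.6%, which reproduces the stated 95%.
- d=0.34, 255 completers: SE = 0.125 and power 77.5%. With all 300: 83.8%. The stated 80% lies between the two; 80% needs 272 completers.
- Within-subject, d=0.34, 95% power: a paired test needs 115 pairs, and 115/0.85 = 135.3, or 136 rounded up, as stated. Here d is on the SD of change.

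The between-group figures therefore behave like a two-sample calculation with no correlation term.

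**Step 2: variance of the two contrasts** (one follow-up, outcome variance 1).
- Difference in changes: 2(1 − r).
- Baseline-adjusted: 1 − r².
- Ratio: 2(1 − r)/[(1 − r)(1 + r)] = 2/(1 + r), which exceeds 1 for every r below 1.

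The ratio is 2/1.3 = 1.54 at r=0.3, 2/1.5 = 1.33 at r=0.5 and 2/1.7 = 1.18 at r=0.7. Equivalently, adjustment gives the same precision with 35%, 25% or 15% fewer participants.

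**Step 3: the three-visit mixed model.** Generalized least squares, 150 per arm, equal correlation r between visits, 15% missing at 1 week, arm contrast at 1 week, d=0.34 in raw SD units, power = Φ(0.34/SE − 1.96):

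| r | SE, free baseline means | Power | SE, common baseline mean | Power |
|---|---|---|---|---|
| 0.3 | 0.1439 | 65.7% | 0.1190 | 81.5% |
| 0.4 | 0.1335 | 72.2% | 0.1141 | 84.6% |
| 0.5 | 0.1221 | 79.5% | 0.1076 | 88.5% |
| 0.6 | 0.1094 | 87.5% | 0.0991 | 92.9% |
| 0.7 | 0.0949 | 94.8% | 0.0883 | 97.1% |

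**Step 4: d in change-SD units** (one follow-up, 255 completers). The planned contrast has 77.5% power at every r. Adjustment raises the effective d to 0.34 × √(2/(1 + r)): 0.422 at r=0.3 (power 92%), 0.393 at r=0.5 (88%) and 0.369 at r=0.7 (84%). The gain is present on either scale.

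**Step 5: averaging both follow-ups** (raw SD units, equal correlations, 255 completers). Without adjustment, power is 75.5% at r=0.3 and 81.6% at r=0.4; with adjustment it is 95.2% and 95.9%. The shortfall shrinks but the advantage of adjusting does not.

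**The case against.** The strongest reply is that the article nowhere says the baseline arm means are left free. A model with a common baseline mean also has baseline as a response and arm-by-time terms, so the text is compatible with it, and such detail is often left to an analysis plan. This stands in part: the free baseline is an inference. It is nevertheless the ordinary reading of an interaction test with baseline among the responses, nothing states a constraint, and if one was intended a single sentence settles the matter.

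A reader might go further and infer that the trial has less power than it claims. The documents do not support that as a general statement. It needs both r below 0.5 and d in raw SD units. With single 1-to-5 items a modest r is plausible, but the same items are repeated immediately and after one week, and nothing in the article favours a low value over a higher one. At r=0.6 the planned test has more than the stated 80%. On the change-SD scale, which is how the article's own within-subject figure reproduces, a two-sample calculation is the correct one for the interaction and r drops out. The remaining gap of about 2.5 points at d=0.34 then has nothing to do with baseline handling.

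Two further limits also stand. The figures apply to the Likert outcomes under a linear model and not to the yes/no/unsure item on use of digital tools, where existing use is already a named covariate. And leaving the K-CAT score out of the covariates is not an error: no gain from including it can be quantified from the article, and randomized teens are already restricted to scores above 29.

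**Conclusion.** The point holds as one of efficiency. As the arm comparison is written, and read in the ordinary way, it is a difference in changes, with variance 2/(1+r) times that of a baseline-adjusted contrast in the two-visit case. In a three-visit model at d=0.34 in raw SD units, a common baseline mean raises power by about 16 points at r=0.3, 9 points at r=0.5 and 5 points at r=0.6.

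Whether the planned test misses the stated 80% by a clear margin cannot be decided from the article, because r and the scale of d are not given. It does so in raw SD units with r below 0.5; in change-SD units it has about 77% whatever r is. The planned contrast is unbiased, so this is not an error that distorts the result. Since the baseline score is already measured in everyone before allocation, the improvement is worth making even in a pilot. All figures assume 1:1 allocation, a two-sided 5% test and equal correlations between visits.

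**What to change.** For the three Likert outcomes, state that the mixed model treats time as categorical and gives both arms a common baseline mean (no arm term at baseline). Alternatively, model the two follow-ups as responses with the baseline score of the same item as covariate. Name the arm difference at 1 week as the reported contrast.

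In the power section, state the SD by which d is divided and the assumed baseline-to-follow-up correlation, and recompute the between-group figures for that contrast. The K-CAT score may be added as a covariate, but this is optional.

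The cost is analysis wording and a short recalculation. No new measurement or visit is needed, because the baseline items are already part of the schedule. The article describes recruitment as still under way, so the wording should be fixed before outcomes are compared by arm.
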